### Unfavorable events

Unfavorable events are presently not predicted, due to the study and intervention’s nature.

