## Introduction

Sexual assault against women is an important public health and human rights issue with heterogeneous prevalence around the world [1]. Social inequalities and the cultural structures of societies play a role in the creation, perpetuation and survival of this issue [2]. Although the formation provided by virtual campaigns and the sharing of victims' experiences has increased public awareness of the problems and complications of sexual assault in recent years [3], in countries such as Iran, victims experience a very high psychological and social burden. This is because these individuals are not only the victims of an act of violence, but also bear the social pressure caused by the taboo of sexual assault taboo in society. In many cases, these victims do not report the assault to legal and health authorities and are therefore deprived of sexual health preventive measures. There are no clear and official statistics and information on sexual assault and physical abuse in Iran. More than 80% of cases of sexual harassment go unreported and the real statistics are higher than the published statistics [4]. According to the National Sexual Violence Resource Center, one in five American women will experience sexual assault at some point in her life [5]. Khoramin et al. indicated in a study that the prevalence of post-traumatic stress disorder in rape victims referred to forensic medicine in Kohgiluyeh and Boyar Ahmad provinces was almost 92% [6]. The results of the research on post-traumatic stress disorder among those referred to forensic centers in Tehran indicated that the rate of post-traumatic stress disorder and the rate of depression were respectively, 61.6% and 47.7% among the survivors [7]. The high psychological burden of rape, together with complications such as pregnancy and chronic conditions such as chronic pelvic pain, is associated with an increase in mental disorders. In cases where women have experienced more severe assaults, they show more symptoms of psychological distress [8]. Therefore, sexual assault as a crisis-causing event is associated with post-traumatic stress disorder, a complication that hinders the follow-up of diagnostic and therapeutic measures in victims [9]. In addition to the disturbed mental state of the victims, other factors also fuel this problem. Research has shown that there is a low level of awareness of sexually transmitted infections among the rape survivors attending the forensic medical centers. Based on the results of this study, 59% of the participants had no knowledge of the nature, mode of transmission and prevention of sexually transmitted infections, and 24% had low knowledge [10]. These findings show that rape victims in Iran are mostly unaware of the dangers of rape and may not take health-related measures despite the high post-traumatic stress they experience due to the social pressure caused by the taboo of being a rape victim. The interactions of individuals with the legal, medical and healthcare systems and the search for help after an accident have an impact on their mental well-being. Seeking help after the sexual assault is described by victims as a second rape, and many of these victims do not receive comprehensive care [11, 12]. Given the high economic and social burden of sexual assault on individuals and society, it is recommended that guidelines for accessing essential medical, legal, social support and reporting services be provided and established [1, 2]. To prevent post-traumatic stress disorder in 10 women who had recently been sexually assaulted, Fao et al. in a study designed a comparative program between an intervention group that received a cognitive-behavioral program and a control group that underwent an assessment of trauma-related psychological pathology. The results indicated that two months after the rape, women in the intervention group had fewer symptoms of post-traumatic stress disorder, and after five and a half months, the intervention group had less depression than the control group [13]. Other studies have used various methods such as client-centered therapy [14], mental imagery, and reprocessing of nightmares and suicidal thoughts [15] to reduce symptoms of psychological distress and depression in women who have experienced sexual assault. The individual, situational and cultural factors that contribute to the blaming of rape survivors should be considered in the design of studies and interventions [16]. Social Cognitive Theory [SCT] is an important health theory that views behavior as dynamic and influenced by environmental, behavioral and individual factors. Given that rape is a social problem, educational interventions that focus on the interpersonal level, such as those based on social cognitive theory, may be effective in resolving conflicts caused by the psychological pressures of rape on victims. It also appears that the constructs of this theory can be used to change a one's behavior, awareness and ability [17–19]. Investigating the effect of long-term exposure therapy on social support and the symptom severity in patients with post-traumatic stress disorder, Aghmiuni et al. found that the mentioned exposure therapy can alleviate post-traumatic stress disorder [20]. Studies in Western societies have shown that social support is an effective factor in reducing symptoms of post-traumatic stress disorder caused by sexual assault [21–23]. Cultural factors, economic conditions, family situation, existing legal/punitive systems [24] and the different societal views of women who have experienced sexual assault in Western and traditional societies are among the factors that make the impact of social support different. This is because the disclosure of this incident may expose women who have experienced sexual assault in traditional societies to particular social challenges and social stigma, thus questioning the impact of social support on PTSD in traditional societies [25]. Various measures have been taken to reduce the symptoms and severity of post-traumatic stress disorder. However, there is a continuing need for training programs and more research into post-traumatic stress disorder caused by the experience of sexual assault. The reduction of violence against women and its complications and the achievement of gender equality are among the world's development goals. Awareness-raising and training of women is one of the key aspects in achieving this goal. The aim of the present research is to determine the effect of an educational intervention on post-traumatic stress disorder and social cognitive theory constructs in women who have experienced sexual assault. In case of appropriate impact, the study can be used as an intervention to reduce individual and social complications, and economic costs. It can also promote health behavior change and the management of post-traumatic stress disorder, and encourage healthcare-seeking, thereby improving the quality of life of women who have been raped. This study determines and compares the background characteristics and the mean scores of post-traumatic stress, awareness, health-related attitudes and behaviors, perceived social support, and self-efficacy in and between two intervention and control groups before and two months after the intervention.

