### Study design

This study is randomized, double-blind clinical trial research that will be conducted on 40 women with experience of sexual assault referred to Iran-Isfahan Welfare and Forensic Medicine Centers. In the first phase of the educational intervention, the program, content and questionnaire will be designed and compiled, and in the second phase, sampling will be performed in the form of a census and, then, training sessions will be held. For the purpose of randomization, table of random numbers will be used for two intervention and control groups with a ratio of 1:1. The design of this clinical trial follows the requirements of the CONSORT statement.

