#### Inclusion criteria

Women aged 18–45 years.Women with at least one experience of sexual assault with an interval of at least one month from the incident [if there are symptoms of the disorder, no maximum], and obtained a score of 33 and above in PCL-5 questionnaire with the ability to diagnose based on the DSM-5 diagnostic system and the PTSD was confirmed in them by a clinical psychologist.No current drug use.No current major brain disease.No mental retardation.No major psychiatric disorder.No treatment process.No psychiatric history.No psychiatric record [psychotic disorders: psychosis, bipolar disorder, schizophrenia, bipolar I disorder with psychotic symptoms, dementia], and no pregnancy at study entry.

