#### Exclusion criteria

Missing more than one training session.Experiencing another crisis during the study [mourning the death of a loved one, pregnancy, bankruptcy of the loved ones] were the exclusion criteria.

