Post-traumatic stress disorder in the present study refers to a score confirmed by the PLC-5 questionnaire and the opinion of a clinical psychologist. The PCL-5 is a self-report psychometric measure of PTSD symptoms according to the DSM-5, developed by Weds et al. [29]. The PCL-5 is a 20-item questionnaire, with a 5-point Likert scale (0–4) including 0( not at all), 1 (a little bit), 2 (moderately), 3 (quite a lot) and 4 (extremely) and the total score is calculated with a range of 0–80. Higher scores indicate a greater degree of severity of PTSD in the individual. The validity and reliability of the Persian version was assessed and confirmed by Vermaghani et al. in Iran. The optimal cut-off points for identifying possible positive cases of PTSD in the Iranian population are considered to be 33 [30]. The Cronbach's alpha of the English version of this instrument is 0.95 and the French version is 0.94. The validity and reliability of this instrument in Iran was assessed by Vermaghani et al., and the Cronbach's alpha coefficient for the Persian version was reported to be 0.92 [31, 32]. The questionnaire has been validated by the research team. An example of a checklist item is "extremely negative emotions such as fear, anger, guilt and shame", which is determined by a score of 0 to 4.

Self-efficacy in this research is the score that participants will receive on the General Self-Efficacy Scale (GSE-10). This questionnaire was developed and revised by Schwarzer and Jerusalem with the aim of assessing general self-efficacy [33, 34]. This questionnaire was implemented in Iran by Rajabi [35] on 587 students of Shahid Chamran University of Ahvaz and Marvdasht University. This scale has 10 items on a Likert scale from 1 to 4, with the lowest and highest scores being 10 and 40, respectively. The scale is used to predict adjustment after life transitions or as an index of how life is going at each stage of development, for clinical work and for behavior modification. The Cronbach's alpha coefficient of the GSE-10 scale in Iran is 0.84, which is higher than the standard in different countries, suggesting that it has a high reliability. A sample item of the scale is "If I try hard enough, I can always solve difficult problems", which is measured on a Likert scale of 1–4 ranging from "completely true" to "not true at all".

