To measure the health-related awareness, attitudes and functioning, a researcher-made questionnaire was designed and developed using articles and psychology books. This questionnaire contains 21 items and includes 7 questions on awareness, 7 questions on attitudes and 7 questions on functioning in relation to health. To assess validity and reliability of the questionnaire, the final review will be conducted by 11 professors from Isfahan School of Nursing and Midwifery, Department of Health Psychology, Social and Forensic Medicine, and an epidemiologist. For example, a health-related awareness question is "There are drugs that can prevent the occurrence of sexually transmitted infections" that is scored 1 for a correct answer and 0 for an incorrect answer and I don't know. A health-related item of attitudes is "I am afraid to talk about sexual assault with my relatives", which is measured on a 5-point Likert scale. An example of a health-related behavior item is "To check for complications after rape, I do a genital examination", which is measured using a 4-point Likert scale. Data collection will be performed using a questionnaire on demographic characteristics, GSE-10 self-efficacy questionnaire, a questionnaire on perceived social support, PCL-5 post-traumatic stress disorder questionnaire, and a researcher-made questionnaire on health-related awareness, attitude and behavior. If the research samples did not have a correct understanding of the meaning of the word at the time of completing the questionnaire, it would be explained to them by the questioner.

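### The article dismisses unfavourable events because of the study's nature, describes no recording of them, and has an attendance exclusion that in practice acts in one arm only

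*Protocol article*

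**What the plan says.** The Unfavorable events section is a single sentence: "Unfavorable events are presently not predicted", and the only reason it gives is the nature of the study and of the intervention. The article describes no procedure for asking about, recording or reporting harms.

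Other sections bear on this:

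- **Population (Inclusion criteria).** Women qualify if they "obtained a score of 33 and above in PCL-5 questionnaire" and a clinical psychologist has confirmed PTSD.
- **Measures (Data collection tools and methods).** These are demographics, self-efficacy, perceived social support, and the "PCL-5 post-traumatic stress disorder questionnaire, and a researcher-made questionnaire on health-related awareness, attitude and behavior". On the PCL-5, "Higher scores indicate a greater degree of severity of PTSD in the individual".
- **Timing and contact (Second phase).** There is one pre-test and one post-test two months after the sessions end. Contact in between is as needed, to answer questions.
- **Delivery (Second phase).** The intervention has six weekly sessions, in groups or individually, with brochures that women may pass to supporters, and a virtual group and SMS afterwards. Controls get a single one-hour session.
- **Exclusion criteria.** Women are excluded for absence from more than one session, or for "Experiencing another crisis during the study" (bereavement, pregnancy, bankruptcy of loved ones). Both rules act after randomisation.

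**The concern.** A condensed article may leave harms procedures to a fuller protocol. This one goes further and states a premise, that the nature of the work makes unfavourable events unforeseeable. That premise conflicts with the article's own account of its participants and of the social cost of disclosure.

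Two things are at stake. First, a woman upset by the sessions, or exposed because a brochure or message was seen, would appear in none of the listed measures. Second, the attendance rule could remove a woman who stops coming because of distress, and it has no practical counterpart among controls. The comparison on PCL-5 could then favour the intervention through selective loss, and the report would hold no information from which a reader could detect this.

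**Working it through.** **1. The plan's own figure (not disputed; it sets the denominators).** The Sample size section gives SDs of 7.95 and 8.06, a difference of 7.5, alpha 0.05 and beta 0.2.

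- Pooled SD = √[(7.95² + 8.06²)/2] = 8.005.
- n = 2 × [8.005 × (1.960 + 0.842)/7.5]² = 17.88, so 18 per group (two-sided alpha).
- With 10% drop-out, 18/0.90 = 20 per group. Both stated figures reproduce.

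**2. What the listed measures could detect.**

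- Worsening of PTSD symptoms: yes, by PCL-5 in both arms, for women who reach the post-test.
- Fall in self-efficacy or perceived support: yes, on the same condition.
- Distress caused by sessions: no item described.
- Harm following disclosure: no item described.
- Reason for stopping: no item described.

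**3. Who can meet the attendance rule.** The intervention arm has six sessions, so two absences meet it. The Second phase section gives controls one session, so more than one absence cannot occur. The Control group section mentions continuing training on follow-up of sexually transmitted infections, but gives no number of sessions.

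**4. What recording could show (harm rates are assumptions).** The chance of at least one event among 20 women is 1 − (1 − p)^20:

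- p = 5%: 64%
- p = 10%: 88%
- p = 20%: 99%

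This applies only if events are recorded. With zero recorded events, the one-sided 95% upper bound is 1 − 0.05^(1/20) = 13.9%, or 1 − 0.05^(1/18) = 15.3% with 18 women.

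**5. What exclusion could hide (illustration).** Suppose every harmed woman in the intervention arm is excluded for absence and not measured. Suppose also that the others improve by 7.5 points and the harmed women worsen by 10.

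- 2 of 20 harmed: observed 0/18 against a true 10%. Mean change over all 20 = (−7.5 × 18 + 10 × 2)/20 = −5.75, against −7.5 after exclusion.
- 4 of 20 harmed: observed 0/16 against a true 20%. Mean change = (−7.5 × 16 + 10 × 4)/20 = −4.0, against −7.5.

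**6. Why a margin is needed for PCL-5 worsening.** With no true change, about half of women would score higher at post-test by noise alone. Take 8.005 as the SD at each time, normal scores and an assumed pre–post correlation r. The SD of change is then 8.005 × √[2(1 − r)]. The share rising by more than 7.5 points with no true change is:

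- r = 0.3: SD 9.47, 21%
- r = 0.5: SD 8.01, 17%
- r = 0.7: SD 6.20, 11%

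A margin reduces the noise but does not remove it, so the count must be read against the control arm.

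**The case against.** The strongest reply is that not predicting events differs from not recording them, and that procedures for harms usually sit in a full protocol, which is not shown. This stands as far as it goes. The article's silence does not prove that nothing will be collected, and silence alone would be no finding. It does not defend the stated premise, which the rest of the article undercuts.

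A reader might infer that the trial collects no harms and can report only benefit. The documents do not support that. PCL-5 is scored so that higher is worse, it is taken before and after in both arms, and nothing in the Analysis section limits the comparison to improvement.

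A reader might also infer that the exclusions drop the women most likely to be harmed. That too goes beyond the text. The listed crises are outside events that can occur in either arm, sessions are missed for many reasons, and the article does not say whether excluded women are still measured or analysed.

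Three further supports are weak:

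- The Introduction mentions suicidal thoughts as a target of another therapy, not as an effect of education.
- Its remark that "Seeking help after the sexual assault is described by victims as a second rape" concerns legal, medical and healthcare contacts, not a teaching programme.
- The statement that "The design of this clinical trial follows the requirements of the CONSORT statement" adds nothing here, because the documents do not set out what CONSORT asks on harms.

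Finally, the 14% bound is correct but holds for any arm of 20. It measures how little a zero count would reassure, not a fault in this plan.

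**Conclusion.** The point holds in a limited form. The article states that unfavourable events are not foreseen, gives only the nature of the study as the reason, and describes no recording of harms. This sits badly with a population in which PTSD is confirmed, with its own warning about stigma after disclosure, and with an intervention that creates routes to disclosure. PCL-5 covers symptom worsening in women who are retained. Session-related distress, harm from disclosure and reasons for stopping are not covered by any measure described.

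The attendance exclusion is one-sided in practice and could remove distressed women from the intervention arm alone. This rests on the single control session in the Second phase section and on excluded women not being measured, which the article leaves open. The size of any bias cannot be derived from the documents. The figures for 2 or 4 excluded women are illustrations under assumed rates. The change is worth making because it is cheap, although it will not yield usable harm rates.

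**What to change.** Replace the sentence in Unfavorable events with a statement that harms are possible and will be recorded identically in both arms. In detail:

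1. **At the planned post-test**, add a few set questions on distress from sessions and on harm from disclosure, worded to fit both arms. Self-completion after the PCL-5 would protect both the blinding and the main outcome.
2. **Record the reason for every stop**, in both arms.
3. **Invite all randomised women to the post-test**, including those who meet an exclusion criterion during the study.
4. **Report by arm** the distribution of PCL-5 change and the number worsening by at least a margin fixed in advance. The plan's own 7.5 points is one example, though it was set as a difference between groups and not as a threshold for an individual. Do not count any rise as harm.
5. **List events volunteered at sessions or by telephone separately.** Contact is unequal (six sessions against one, then only as needed), so pooling them would find more harm in the intervention arm simply because those women are seen more often.

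How such reports are handled clinically is for the study team to define.

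The cost is a few added questions and one table, with no new visits. Women who have stopped may decline the post-test, so the number invited and the number measured should be shown by arm. Counts will remain too small to estimate rates and should be presented as such.

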### Analysis

All statistical trials and confidence intervals will be supposed with a type I error established in alpha = 0.05, using the IBM SPSS V26 statistics package. The data in this research are of a quantitative and qualitative nature, and descriptive and inferential statistical methods are used for analysis. In order to achieve the research question, determine and compare the demographic characteristics (field) between the two test and control groups, from descriptive statistics tests, independent t-test for quantitative variables such as age and number of family members, for nominal qualitative variables such as occupation. Chi-square test was used and Mann–Whitney test was used for the qualitative variable, level of education, type of residence, child's birth rate. In order to achieve the objectives of the research, the analysis of variance with repeated measures will be used to investigate the main and combined effects, and then the Bonferroni post hoc test will be used to answer the objectives (comparison within each group) and objectives (comparison between two groups).

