### Sample size

According to the mean values and standard deviation before and after the educational intervention in previous studies [26] and asking the opinions of statistics experts and considering α = 0.05 and β = 0.2, the standard deviations of 7.95 and 8.06 in the intervention and control groups, and a minimum difference of 7.5 points between the two groups in terms of post-traumatic stress disorder, the sample size is calculated to be 18 participants in each group. However, considering a drop-out rate of 10%, the sample size is set at 20 participants in each group.

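### Repeated-measures ANOVA with post hoc tests leaves the deciding test open and does not adjust for baseline PCL-5; one baseline-adjusted between-arm comparison would be better at no cost

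*Protocol article*

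**What the plan says.** The Analysis section of the protocol article specifies "the analysis of variance with repeated measures will be used to investigate the main and combined effects, and then the Bonferroni post hoc test". It directs the post hoc step at two kinds of aim, listed as "objectives (comparison within each group) and objectives (comparison between two groups"). The aims under Methods/design, and the account of the second phase of the intervention, give two arms and two measurement times: a pre-test, and a post-test two months after the last session.

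The Sample size section sets the error rates by "considering α = 0.05 and β = 0.2". For the spread of scores it uses "the standard deviations of 7.95 and 8.06 in the intervention and control groups". Its target effect is "a minimum difference of 7.5 points between the two groups in terms of post-traumatic stress disorder". It arrives at 18 per arm, raised to 20 for 10% drop-out. It does not say whether the SDs belong to the post-test score or to the change from baseline, and it gives no pre/post correlation.

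The Inclusion criteria admit women at least one month after the assault who have "obtained a score of 33 and above in PCL-5 questionnaire". Every participant therefore has a baseline value of the main outcome scale.

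**The concern.** With two arms and two times, the plan produces several different tests, and they do not answer the same question.

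- **Group main effect.** It averages the pre-test, where randomised arms differ only by chance, with the post-test. It estimates half the treatment effect.
- **Time main effect and within-arm tests.** They describe change over time and do not compare the arms. Women enter on a high score, from one month after the assault. Regression to the mean and natural recovery can lower scores in both arms without any effect of training.
- **Group-by-time interaction (the combined effect).** It is a valid test of the treatment effect. With two times it is the t-test on change scores, which is less precise than adjusting for baseline.
- **Between-arm post hoc comparison at follow-up.** It is also valid, but it ignores the baseline.

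The section does not say which of these settles whether the training worked. At stake are precision in a 40-woman trial and the clarity of its conclusion.

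**Working it through.** **Inputs.** From the Sample size section: α = 0.05, β = 0.2, SDs 7.95 and 8.06, difference 7.5, 18 evaluable per arm. Allocation is 1:1 (Study design). Assumed: two-sided testing, equal pre- and post-test SDs, and pre/post correlation ρ of 0.3, 0.5 and 0.7.

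**1. The plan's own figure.** Pooled SD = √[(7.95² + 8.06²)/2] = 8.005. n = 2(1.960 + 0.842)² × 8.005² / 7.5² = 17.88, so 18 per arm; 18/0.9 = 20. The stated size reproduces as a two-sample comparison of means. Normal-approximation power at 18 is 80.3%; t-test power is 78.0% at 18 and 82.3% at 20.

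**2. What each test estimates, and its SD** (σ = SD of a single score):

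- Post-test only: 7.5, SD σ.
- Interaction (change score): 7.5, SD σ√[2(1−ρ)].
- Group main effect: 7.5/2 = 3.75, SD σ√[(1+ρ)/2].
- ANCOVA on baseline: 7.5, SD σ√(1−ρ²).

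The change-score variance is 2(1−ρ)/(1−ρ²) = 2/(1+ρ) times the ANCOVA variance: 1.54, 1.33 and 1.18 times.

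**3. Power at 18 per arm if 7.95/8.06 are post-score SDs (σ = 8.005).** Noncentral t with 34 df, or 33 for ANCOVA.

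| Test | ρ = 0.3 | ρ = 0.5 | ρ = 0.7 |
|---|---|---|---|
| ANCOVA | 82% | 88% | 97% |
| Interaction | 64% | 78% | 94% |
| Post-test only | 78% | 78% | 78% |
| Group main effect | 40% | 35% | 32% |

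The ANCOVA formula ignores the small cost of chance baseline imbalance. A simulation of 40,000 trials per setting, which includes it, gives ANCOVA about 80%, 87% and 96–97%.

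**4. Power if they are change-score SDs.** Then σ = 8.005/√[2(1−ρ)] = 6.77, 8.01 and 10.33.

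| Test | ρ = 0.3 | ρ = 0.5 | ρ = 0.7 |
|---|---|---|---|
| ANCOVA | 92% | 88% | 84% |
| Interaction | 78% | 78% | 78% |
| Post-test only | 90% | 78% | 56% |
| Group main effect | 52% | 35% | 21% |

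**5. Within-arm tests.** Assume no treatment effect and a 4-point fall in both arms (an illustrative figure; the protocol article gives none). A paired t-test with n = 18 and SD 8.005√[2(1−ρ)] = 9.47, 8.01 and 6.20 is significant within an arm 39%, 52% and 73% of the time. In simulation, a significant fall in the intervention arm without one in the control arm occurs in 24%, 25% and 20% of such trials.

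**6. Bonferroni.** Two times give one before/after contrast per arm, and two arms give one between-arm contrast per time. A family of one contrast receives no correction.

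**7. An open choice of test.** Under no effect of any kind, each between-arm test rejects about 5% of the time. If a significant result on any of the interaction, the group main effect or the post-test comparison counted as success, simulation gives 11–12%.

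**The case against.** The strongest reply is that the plan already contains sound tests. The ANOVA is there to investigate effects, and the post hoc comparisons are what answer the objectives. A between-arm comparison at follow-up is the natural reading of one of them, and it is the test that the Sample size section sizes. In a randomised trial that comparison and the interaction are each unbiased and hold 5%. All of this stands.

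Two stronger readings are therefore tempting but unsupported. A reader might infer that the 80% power belongs to a test the plan never names. It does not: the between-arm post hoc test at follow-up matches it at any correlation, and if the SDs are change-score SDs the interaction matches it too. A reader might also infer that the group main effect or a within-arm fall will be reported as the trial result. The text does not say so; it only fails to rule it out.

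The size of the gain is also open to challenge. The correlation is not given, and the entry cut-off may narrow the baseline spread. If, as an assumption, selection cuts the baseline SD to 0.7 of its unselected value and leaves the residual variance unchanged, the variance ratio becomes 1 + 0.49(1−ρ)/(1+ρ) = 1.26, 1.16 and 1.09. Interaction power is then about 72%, 83% and 96%, against 82%, 88% and 97% for ANCOVA. The gain shrinks but does not reverse.

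A fuller analysis plan may add detail. This point, however, concerns a method that the article states.

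**Conclusion.** The concern holds as one of efficiency and targeting. The plan does not say which test decides efficacy, does not use the baseline PCL-5 to sharpen the comparison, and includes within-arm tests among those that answer the objectives although they carry no evidence of a treatment effect.

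Over the interaction, ANCOVA gains about 18, 10 and 3 percentage points of power at ρ = 0.3, 0.5 and 0.7 with post-score SDs, and about 14, 10 and 6 with change-score SDs. Over the post-test alone the gain with post-score SDs is about 4, 10 and 19 points; it is close to nothing at ρ of 0.2 or less. Beyond a trivial small-sample cost at very low ρ, ANCOVA is no less powerful than any planned between-arm test under either reading.

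These sizes rest on an assumed correlation, and the within-arm figures also on an assumed 4-point fall. The documents do not support calling the analysis invalid or the sample size wrong.

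**What to change.** State one primary analysis: the between-arm difference in two-month PCL-5 total from a linear model with arm and baseline PCL-5, reported with its 95% CI. Use the same form of model, each with its own baseline, for self-efficacy, perceived social support, and health-related awareness, attitude and behaviour. Report within-arm changes descriptively, and do not use them or the group main effect as evidence of efficacy. The Bonferroni step within an outcome can go.

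The Sample size section should also say whether 7.95 and 8.06 are post-score or change-score SDs. The cost is a paragraph of wording. The data and software stay the same, and 18 per arm raised to 20 stands.
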